4. **Statistical Considerations:** Describe the statistical analyses that support the study design.

**Statistical Analyses: Exercise vs. health education study.** We will perform Analysis of Covariance (ANCOVA), with each woman's change in outcome (final value – baseline) modeled as a function of treatment group. Each variable listed in the Primary Aims section above will be examined in this fashion. The hypotheses will be tested according to the intention-to-treat philosophy in which all randomized participants will be grouped according to their intervention assignment at randomization, regardless of compliance or adherence to the study. Secondly, mixed effects models for correlated outcomes will also be used to model the data collected on the absolute change in the outcome measures using all time-point differences. Prior to fitting these models, we will perform exploratory data analyses focusing on the distributions of hormone levels by time and intervention group, assessing the appropriateness of log-transformation. Age, prediagnosis menopausal status, race/ethnicity, baseline BMI, and disease stage will be examined as potential covariates to be included in multi-variable adjusted analyses. Among women randomized to exercise, we will also examine effects of exercise on endpoints stratified by adherence (assessed from the DALs) and other measures of compliance (pedometers and PAQ). To explore the potential for effect modification, we will consider stratifying the effect of exercise on endpoints by menopausal status. Two-sided tests will be used for significance. From the food frequency questionnaires, we will identify participants who change their total caloric intake during the study period, and will assess the effect of exercise on outcomes, controlling for change in total caloric intake. Since we are assessing multiple secondary outcomes, we will consider using Bonferroni correction. Although we do not anticipate an appreciable number of participants lost-to-follow-up because of our plan for tracking participants our plan for missing data handling is as follows. The primary mixed model analyses will be performed using all available data, which assumes missing data are missing at random (86). Under this mechanism, the probability of lost-to-follow-up depends on the observed data. Non-random or informative lost-to-follow-up occurs when there is a correlation between the probability of lost-to-follow-up and missing data.

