**Power and Sample Size Considerations:** With a sample size of 230 (which accounts for a potential 30% drop-out/lost to follow up rate) we will have at least 80% power to examine the effect of exercise on QOL and circulating hormones. Our exercise interventions in breast cancer survivors have yielded attrition rates of ~ 10%. Exercise interventions in other cancer survivors (e.g., colon, prostate, and lymphoma) have also yielded similar attrition rates. We hypothesize that attrition may be slightly greater (i.e., 20%) in ovarian cancer patients given their potential for advanced disease, worse QOL and reduced prognosis. However, because no exercise trial has been conducted in ovarian cancer survivors, we now plan to over-recruit to account for a potentially higher attrition rate (30%), and have therefore increased our sample size to N = 230.

In our exercise trial in postmenopausal women, QOL measured by SF-36 was  $79.95 \pm 14.88$  (72). Assuming a 10% effect size, we would need 54 subjects per group or 108 in total. Taking a 30% potential drop-out rate into consideration, then a sample size of 155 is necessary. A 10% between group effect size was observed in Courneya and colleagues recent publication of physical activity and QOL in ovarian cancer survivors (10). A difference of 10 points is clinically meaningful given a recent chemotherapy trial reported an increase of 10 points in QOL, suggesting that 10 points represents a

meaningful improvement in QOL (37). For insulin, Ligibel recently showed a 28% effect size (2.9  $\mu$ U/mL) and standard deviation of 8.0  $\mu$ U/mL, which yields a per group sample size of 80 or total N = 160 (71). Considering the potential for a 30% drop-out with a sample size of 230, a sample size with complete data on 160 women will provide at least 80% power for insulin. For the other hormones, if we assume a 20% effect size, then based on means and standard deviations of these hormones in ovarian cancer survivors (18-20,22,23,47,48,50-55), a sample size of 230 will provide 80% power.

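### The insulin sample size does not follow from its stated inputs: a 2.9 µU/mL difference with SD 8.0 needs about 121 completers per group, and 80 per group gives about 62% power, not at least 80%

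*Protocol*

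**What the plan says.** The relevant text is in the protocol, section 4 (Statistical Considerations), under Power and Sample Size Considerations.

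- The opening sentence covers all the markers: with 230 women, a number said to allow for 30% drop-out, "we will have at least 80% power to examine the effect of exercise on QOL and circulating hormones".
- For insulin, the protocol relies on a cited exercise trial that "recently showed a 28% effect size (2.9" µU/mL) and a "standard deviation of 8.0" µU/mL, "which yields a per group sample size of 80 or total N = 160".
- It then applies 30% drop-out to 230 and concludes that "a sample size with complete data on 160 women will provide at least 80% power for insulin".
- The analysis paragraph just before says "Two-sided tests will be used for significance". It models each woman's change from baseline by treatment group. The listed candidate covariates are age, menopausal status, race/ethnicity, baseline BMI and disease stage; the baseline value of the outcome is not among them.

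No numeric alpha is given. The protocol does not say whether 8.0 is the SD of single-visit values or of change, and it states no correlation between visits.

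**The concern.** The standardised difference is 2.9/8.0 = 0.3625, which is modest, and 80 per group is too few to detect it with 80% power in a two-sided test. Insulin is listed among the serum hormones in the Primary Aims. Of the two worked calculations, it is also the one that matches the final N: 160/0.70 = 229, against 155 for quality of life. The stated power is therefore part of the justification for 230. If it stands, a null insulin result could be reported as coming from a test with at least 80% power, when the chance of missing the assumed effect was appreciably larger than 20%.

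**Working it through.** **Inputs.** Difference 2.9 µU/mL, SD 8.0 µU/mL, 80 per group, 30% drop-out, target power 80% (all from Power and Sample Size Considerations); two-sided testing (Statistical Analyses); 1:1 allocation, 115 per group (D.8). Alpha = 0.05 is an assumption, checked in step 1.

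**Step 1. Which convention did the protocol use?** The quality-of-life calculation allows a check: "Assuming a 10% effect size, we would need 54 subjects per group or 108 in total", with mean 79.95 and SD 14.88. A 10% difference is 7.995. With z-values 1.960 and 0.842 (sum 2.802, squared 7.849):

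n per group = 2 × 7.849 × (14.88/7.995)² = 54.4.

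This matches the stated 54 (55 if rounded up). A one-sided 5% test would need 43. So the protocol's own figure fits two-sided 5% and 80% power.

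**Step 2. The same formula for insulin.**

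n per group = 2 × 7.849 × (8.0/2.9)² = 119.5, so 120.

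The t-test calculation gives 120.4, so 121 per group, or 242 completers. The stated figure of 80 is not reproduced.

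**Step 3. Could another convention give 80?**

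- One-sided 5% (same as two-sided 10%): 95 per group.
- One-sided 10%: 69 per group.
- Two-sided 5% with 90% power: 160 per group.

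None gives 80 per group. With two-sided 5% and 80% power, 80 per group would need an SD of about 6.5 instead of 8.0, or a difference of about 3.6 instead of 2.9. The drop-out step is correct (230 × 0.70 = 161; 160/0.70 = 229), so the error lies in the 80.

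**Step 4. Power on the stated inputs (t test, two-sided 5%).**

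| Completers per group | Situation | Power |
|---|---|---|
| 80 | 30% attrition | 62.5% |
| 92 | 20% attrition (115 × 0.80) | 68.6% |
| 115 | no attrition | 78.1% |
| 121 | needed for 80% | 80.2% |

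The normal approximation gives 63.0%, 69.1% and 78.5% for the first three rows.

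**Step 5. Detectable difference at 80 per group.** The standardised difference with 80% power is 0.4457, so 0.4457 × 8.0 = 3.57, about 3.6 µU/mL.

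**Step 6. What correlation would rescue 80 per group?** This applies only if 8.0 is a single-visit SD; r is the correlation between baseline and six months. The residual SD must fall to about 6.5, a variance ratio of (0.3625/0.4457)² = 0.66.

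- Baseline value as an ANCOVA covariate: 1 − r² = 0.66, so r of about 0.58 or more.
- Change score without that covariate: 2(1 − r) = 0.66, so r of about 0.67 or more.

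If 8.0 is already the SD of change, an unadjusted change-score analysis gains nothing further.

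**Step 7. The other hormones.** For a 20% effect at 80 completers per group, 80% power requires a coefficient of variation of at most 0.20/0.4457 = 0.45. The document gives no means or SDs for these hormones, so whether they meet this cannot be checked.

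**The case against.** The strongest reply is that the protocol names ANCOVA. If 8.0 is a single-visit SD, adjusting for baseline insulin could restore 80% power at 80 per group. That is possible, but nothing in the text supports it: no correlation is stated, the SD is not identified, and baseline insulin is not among the listed covariates. It is a reason to offer the sponsor that route in the fix, not a defence of the figure as printed.

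Second, 30% attrition is a planning allowance. The protocol hypothesises 20% and elsewhere expects less than 20%. On that expectation power is about 69% or a little more, still well short of the claim.

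Third, insulin is one of ten serum markers, alongside quality of life, body composition and cortisol. That limits the consequences but does not correct the statement. The quality-of-life calculation is unaffected: its inputs give about 92% power at 80 per group.

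Three stronger readings are tempting and should be resisted.

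- A reader might infer that the other hormones are underpowered too. The text, "For the other hormones, if we assume a 20% effect size", rests on means and SDs from cited studies that are not reproduced. Insulin's variability is not evidence about the other markers.
- A reader might infer that the other-hormone figure ignores drop-out because it is quoted at 230. The opening sentence of the same section says that 230 already allows for 30% drop-out, so the figure may include it.
- A reader might infer that 230 women could never give 80% power for insulin. Without attrition the shortfall is under 2 points, and if 8.0 is a single-visit SD, baseline adjustment with a correlation of only about 0.25 would close it.

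**Conclusion.** The insulin calculation is wrong as written. On the stated difference and SD, with two-sided 5% testing, about 121 completers per group are needed, not 80. Power is about 62% at the planned 30% attrition, about 69% at 20%, and about 78% with all 230 women. The chance of missing the assumed effect is therefore about 37.5% at the planned attrition and about 31% at 20%, against the 20% implied. The conclusion rests on one assumption not in the text, alpha = 0.05, which the quality-of-life figure supports; one-sided 5% would still leave about 74% power at 80 per group. It also takes 8.0 as the SD of the quantity analysed, because the protocol offers no other reading.

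The opening claim of at least 80% power for circulating hormones fails because of insulin alone. For the other hormones the claim is unverified, not refuted.

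**What to change.** Keep N = 230 and correct the power paragraph in one of two ways.

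1. Replace the 80 per group and the 80% power claim for insulin with: about 62% power for 2.9 µU/mL (SD 8.0, two-sided 5%) at 80 completers per group, and 80% power for about 3.6 µU/mL. Adding about 69% at 20% attrition would be informative.
2. If there is a basis for 80 per group, state it: the SD of change, or the correlation between baseline and six months together with the model. If 8.0 is a single-visit SD, r must be about 0.58 or more with baseline insulin as an ANCOVA covariate (which must then be listed), or about 0.67 or more for an unadjusted change score.

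In either case state alpha. Unless the second route is taken, also limit the opening sentence so that its 80% claim no longer covers insulin. For the other hormones it is enough to note that a 20% effect has 80% power at 80 completers per group only if the coefficient of variation is at most about 0.45.

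The cost is wording only. No more women are needed; the stated power for insulin becomes less favourable unless the second route can be supported.
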